## Introduction

Glioblastoma is an aggressive primary brain tumor with an unfavorable prognosis. In unselected contemporary cohorts, median overall survival is generally between 12 and 18 months, whereas selected molecular subgroups may experience substantially longer survival [1–3]. It remains among the solid tumors with the shortest survival despite multimodal therapy. Management of newly diagnosed glioblastoma typically includes maximal safe tumor resection, followed by combined radiotherapy and temozolomide chemotherapy. In selected patients, treatment may be supplemented with tumor-treating fields. Since the introduction of radiotherapy plus temozolomide in 2005, only a small number of randomized phase III trials have demonstrated an overall survival benefit in newly diagnosed glioblastoma, largely driven by alkylating regimens rather than targeted or immune therapies [1]. Nearly all patients ultimately develop disease progression despite initial therapy.

At recurrence, management is individualized and may include repeat surgery, reirradiation, and systemic agents, but evidence is heterogeneous and no universally accepted overall-survival–prolonging standard exists [4]. Given the poor prognosis and high neurological morbidity, a glioblastoma diagnosis can profoundly disrupt emotional well-being, physical function, and social roles [5, 6]. Compared with many other cancers, brain tumors uniquely threaten cognition, communication, behavior, and autonomy, complicating decision-making and social participation [7, 8]. Psycho-oncological consultations frequently reveal high psychological burden, with many patients expressing concerns about death and a strong need for medical information [9]. Hence, patients with glioma frequently experience psychiatric comorbidities such as depression and anxiety, which are associated with diminished quality of life and may negatively affect treatment adherence and survival. By comparison, suicidality remains understudied and is rarely assessed in a standardized manner [10–13]. Depressive symptoms may reflect direct neurobiological and treatment-related effects (e.g., lesion location, inflammation, corticosteroid exposure) and/or a psychological response to diagnosis and functional loss [11]. Longitudinal trajectories of depression and anxiety after surgery are heterogeneous, with some patients improving transiently and others worsening as treatment burden and neurological disability accumulate [14, 15].

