Registry-based analyses report low absolute numbers of death by suicide in malignant brain tumor patients, but interpretation is limited by ascertainment, follow-up time, and the fact that suicidal ideation is rarely captured in such datasets. In registry studies, higher suicide mortality has been associated with demographic factors (e.g., male sex and older age) and tumor-related characteristics (e.g., supratentorial location), although findings may reflect confounding and may not generalize across healthcare systems and populations. Adjusted registry models suggest that suicide mortality may be highest within the first year after diagnosis and is associated with age, sex, and tumor location, although causality cannot be inferred [22]. Another U.S. population-based analysis likewise reported that suicide deaths are rare events in brain tumor registries and appear more frequent in older male patients and in glioblastoma, underscoring the need for studies that directly measure suicidal ideation and behavior [23]. A systematic review reported that suicidal ideation is substantially more common than suicide attempts in brain tumor populations [24], but estimates vary widely across studies due to heterogeneous measurement tools, timepoints, and tumor subtypes. Across heterogeneous studies, suicidal ideation and behavior have been associated with depressive and anxiety symptoms, functional impairment, and selected demographic and tumor-related characteristics, although endpoint definitions differ substantially.

However, suicide mortality estimates from administrative registries are vulnerable to misclassification and under-ascertainment, and their generalizability to contemporary Central European healthcare settings remains uncertain. Most datasets also do not assess how many individuals experienced significant suicidal ideation without progressing to recognized suicide.

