Diagnosis of high-grade glioma often causes significant psychosocial stress in affected patients. Even structured distress screening strategies have shown limited impact on downstream psychosocial care uptake, highlighting implementation gaps relevant to mental health risk detection. The GLIOPT study investigated whether screening for distress based on physician–patient conversations was improved in the intervention group compared with the control group, which completed only the Distress Thermometer. In that trial, the endpoint focused on the number of patients with impaired emotional functioning who received specialized psychosocial care, rather than on suicidality-specific outcomes [25]. This underscores that generic distress screening alone may be insufficient to trigger appropriate psychosocial interventions, supporting the need for suicidality-specific assessment in glioblastoma.

Functional impairment in intracranial tumor patients may coincide with greater psychological burden, supporting the inclusion of performance status as a potential correlate of suicidality. In a German longitudinal cohort, 21.5% of participants reported suicidal thoughts at least once during follow-up, although estimates are limited by tumor heterogeneity and measurement approach. Reported suicidal ideation fluctuated over follow-up timepoints, with peaks in some subgroups, but subgroup-specific estimates are difficult to generalize to glioblastoma. That study suggested that suicidal thoughts can occur across different intracranial tumor histologies, alongside reduced health-related quality of life, although generalizability is limited [26]. Against the backdrop of these findings, our planned study will examine suicidality in a multicenter design, focusing on glioblastoma patients, with slightly modified endpoints in light of the current WHO CNS classification.

In summary, depression, anxiety, and suicidality constitute clinically relevant and potentially under-recognized comorbidities in glioblastoma care. Population-based studies suggest increased suicide mortality in malignant brain tumor populations, while suicidal ideation is likely far more prevalent yet less systematically measured. Nevertheless, available data remain limited, and prospective studies are scarce.

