### Sample size calculation

A sample size calculation has been performed for a multiple linear regression analysis with ten candidate predictor domains: marital status (single, married, divorced, or widowed), age (in years), physical impairment (Karnofsky Performance Status), sex (male/female), depression (PHQ-8), anxiety (GAD-7), social support (SUCE−4), health-related quality of life (EORTC QLQ-C30 and EORTC QLQ-BN20), time since diagnosis (in days) and tumor location (brainstem, frontal, parietal, cerebellum, temporal, occipital, basal ganglia, or spinal). An exploratory sample size calculation was conducted for the planned multiple linear regression analysis, including approximately 20 regression parameters, accounting for the use of dummy coding for categorical variables with more than two levels. Based on a medium effect size assumption (f^2^ = 0.15; corresponding to R^2^ ≈ 0.13), an alpha level of 0.05, and a desired statistical power of 0.80, the required sample size was estimated at 157 participants using G*Power. This calculation should be interpreted as exploratory, particularly given the uncertainty regarding the magnitude of the expected effects and the possibility that effects may be smaller than anticipated. Therefore, all analyses will report confidence intervals and effect size estimates alongside significance tests to allow for an informed interpretation of the findings, irrespective of whether medium-sized effects are observed. To account for an anticipated attrition and data loss rate of approximately 15% (e.g., due to incomplete questionnaires, missing covariate data, or exclusions during data cleaning), the planned recruitment target was increased from 157 to 180 participants.

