#### Statistical analyses

Associations between suicidality and candidate predictors will be examined using regression models appropriate to the distribution of the SSEV outcome, defined as the continuous 6-item SSEV composite score assessing suicidal ideation during the past four weeks. Depending on distributional properties, linear regression models will be used for approximately continuous and symmetric outcomes, while generalized models will be considered in case of marked skewness or zero inflation. All assumptions (including linearity, homoscedasticity, and distribution of residuals) will be assessed and reported where applicable. Prior to multivariable modeling, descriptive statistics and bivariate correlations (Pearson or Spearman, depending on scale properties and distribution) will be computed to describe the data structure. These analyses are purely exploratory and will not be used for variable selection. Multicollinearity will be assessed using variance inflation factors (VIF).

As secondary and sensitivity analyses, additional models will be fitted using (a) a dichotomized suicidal ideation outcome (presence vs. absence of suicidal ideation, defined as a 6-item SSEV score ≥ 1) and (b) lifetime suicide attempts assessed by the dedicated dichotomous SSEV item. These analyses will include the same set of predictors and are intended to assess the robustness of findings across alternative operationalizations of suicidality. All analyses are considered exploratory and hypothesis-generating and are not intended to establish causal relationships.

Given the exploratory nature of the study, all prespecified candidate predictors will be entered simultaneously into a multivariable model without prior univariable screening. To reduce overfitting and improve the stability of estimates in the presence of a relatively high number of predictors, penalized regression (ridge regression with tuning via cross-validation) will be applied. Model performance will be internally validated using bootstrap resampling (e.g., 5,000 resamples) to estimate and correct for optimism in performance metrics. Regression coefficients with 95% confidence intervals will be reported, along with model performance measures such as R^2^ and root mean squared error (RMSE) for the continuous outcome.

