## Perspective

This multicenter observational study with a single cross-sectional assessment will estimate the past-4-week frequency and severity of suicidality [28] and examine cross-sectional associations with demographic, clinical, and tumor characteristics in adults with isocitrate dehydrogenase (IDH) wild-type glioblastoma enrolled between initial diagnosis and first recurrence. Depressive and anxiety symptoms are common in glioblastoma. They are associated with shorter overall survival and poorer health-related quality of life in meta-analytic evidence, whereas suicidality in brain tumor populations appears elevated yet remains incompletely characterized beyond registry-based endpoints. However, the literature is dominated by retrospective registry analyses and small single-center cohorts with variable definitions and observation windows for suicidality, often without standardized assessment of suicidal ideation and attempts. In particular, prior datasets often lack granular neuro-oncologic and treatment variables (e.g., functional status, corticosteroid exposure, antiseizure medication, extent of resection, and molecular markers) alongside standardized patient-reported outcomes, limiting confounder adjustment and interpretability.

The primary objective is to model cross-sectional associations between suicidality (SSEV) and depressive symptoms (PHQ-8), anxiety symptoms (GAD-7), and prespecified demographic, clinical, and tumor characteristics. As secondary objectives, the study aims to characterize the distribution of depressive and anxiety symptom severity and to explore how suicidality and overall symptom burden relate to tumor location, functional status as measured by the Karnofsky Performance Score, and perceived social support (SUCE−4) [29].

To achieve these goals, the protocol combines validated patient-reported outcome measures with standardized neurological examination and structured abstraction of treatment and imaging variables across centers.

The study is designed to minimize patient burden by integrating all procedures into a single outpatient visit, while ensuring that data are collected in a standardized manner across multiple centers using a standardized case report form and training before delegation.

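### The only multivariable model described estimates tumor location and KPS after adjustment for depression, anxiety and quality of life, so it may understate the overall associations the study asks about

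*Protocol article*

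**What the plan says.** The section on sample size names the predictor set: "A sample size calculation has been performed for a multiple linear regression analysis with ten candidate predictor domains". These are marital status, age, KPS, sex, PHQ-8, GAD-7, social support (SUCE-4), HRQoL, time since diagnosis and tumor location. Under Statistical analyses, "all prespecified candidate predictors will be entered simultaneously into a multivariable model without prior univariable screening", with ridge penalization. The models for dichotomized ideation and for lifetime attempts reuse the same predictors. No staged or nested model is described.

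Two other places bear on this choice. The Introduction states: "Depressive symptoms may reflect direct neurobiological and treatment-related effects (e.g., lesion location, inflammation, corticosteroid exposure) and/or a psychological response to diagnosis and functional loss". The Perspective sets a secondary objective to "explore how suicidality and overall symptom burden relate to tumor location, functional status as measured by the Karnofsky Performance Score, and perceived social support".

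Before modelling, "bivariate correlations (Pearson or Spearman, depending on scale properties and distribution) will be computed to describe the data structure". These correlations are labelled exploratory and play no part in variable selection.

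**The concern.** A coefficient for location or KPS in the simultaneous model compares patients who have the same PHQ-8, GAD-7 and HRQoL scores. If a frontal lesion or a low KPS raises suicidality partly by causing depression, that part is credited to PHQ-8. What remains for location or KPS is a conditional association, whereas the Perspective asks about the relation as such.

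The risk lies in interpretation. A small location or KPS coefficient from the full model could be read as showing no relation to suicidality, although the factor might still mark patients at higher risk. The Conclusions name support for identifying such patients as an intended use.

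**Working it through.** **Passages side by side.** The Introduction puts depression downstream of lesion location and functional loss, in hedged terms. The Perspective asks about location and KPS. Statistical analyses conditions both on depression, in the main and the secondary models. The question and the coefficient match only if none of the association passes through the adjusted variables.

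**The plan's own figure.** Inputs from the sample size section: f² = 0.15, alpha 0.05, power 0.80, about 20 parameters. The overall F test has 20 and n − 21 degrees of freedom and noncentrality 0.15 × n. The smallest n with power of at least 0.80 is 157 (power 0.803), and R² = 0.15/1.15 = 0.130. The stated 157 is reproduced and is not in dispute.

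**How much could be lost.** The documents give no mediated share, so the following inputs are assumptions: total standardized KPS effect c = 0.30; correlation of KPS with distress a = 0.45; mediated share s from 0 to 100%; other covariates unrelated to KPS; unpenalized least squares; n = 157.

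- Path from distress to suicidality: b = s × c / a
- Adjusted KPS coefficient: c′ = c × (1 − s)
- R² = c′² + b² + 2 × c′ × b × a
- SE = √[(1 − R²) × VIF / (157 − 20 − 1)], with VIF = 1/(1 − 0.45²) = 1.254
- Power = Φ(c′/SE − 1.96) + Φ(−c′/SE − 1.96)

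| Share mediated | b | c′ | R² | SE | Power |
|---|---|---|---|---|---|
| 0% | 0 | 0.300 | 0.090 | 0.092 | 0.91 |
| 25% | 0.167 | 0.225 | 0.112 | 0.090 | 0.70 |
| 50% | 0.333 | 0.150 | 0.179 | 0.087 | 0.41 |
| 75% | 0.500 | 0.075 | 0.289 | 0.081 | 0.15 |
| 100% | 0.667 | 0 | 0.444 | 0.072 | 0.05 |

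Without the distress measures and with 15 parameters, SE = √[(1 − 0.09)/(157 − 15 − 1)] = 0.080. The coefficient is 0.30 and power is about 0.96 in every row.

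A simulation with three error-prone distress measures and 16 other covariates gave a milder loss. The adjusted coefficient was 0.30, 0.24, 0.18, 0.12 and 0.06 down the rows, with power 0.91, 0.77, 0.53, 0.29 and 0.12. The raw KPS correlation stayed at 0.30 throughout. With an assumed total effect of 0.20, power without distress adjustment is 0.67. With adjustment it is 0.30 to 0.41 at 25% mediated and 0.16 to 0.22 at 50%, for a between 0.6 and 0.3.

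**Does a first model fit the planned sample?** Parameters: marital status 3, age 1, KPS 1, sex 1, social support 1, time since diagnosis 1, location 7, total 15. At f² = 0.15 this needs n = 139. With 157 patients power is 0.865. With 180 × 0.85 = 153 it is 0.853.

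The benefit does not come from saved degrees of freedom. For the seven location parameters at a partial f² of 0.05 and n = 157, power is 0.47 with either 15 or 20 parameters. What changes is the quantity estimated.

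**The case against.** The strongest reply is that the study disclaims causal aims and that the joint model suits its primary objective, which includes the associations with PHQ-8 and GAD-7 themselves. That stands, and it is a reason to keep the full model. It does not settle whether a location or KPS coefficient is an overall or a conditional association.

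A second reply is that direction is open in data from a single visit. Low mood could depress a KPS rating or perceived support, and PHQ-8 would then act as a confounder that ought to stay in. This also stands. It argues for showing both models rather than relying on either alone.

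A reader might infer that the protocol itself places anxiety and HRQoL on the path, and has marital status and social support acting through mood. The text does not support this. Only depressive symptoms are linked to lesion location and functional loss, and only as a possibility. Elsewhere the Introduction is weaker still: "Functional impairment in intracranial tumor patients may coincide with greater psychological burden, supporting the inclusion of performance status as a potential correlate of suicidality". It also lists the factors side by side: "suicidal ideation and behavior have been associated with depressive and anxiety symptoms, functional impairment, and selected demographic and tumor-related characteristics".

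A reader might also infer that the plan conceals these associations altogether. It does not, because the bivariate correlations would show the raw relation of suicidality with KPS and SUCE-4. They are only a partial answer: they are descriptive, unadjusted for age and sex, and Pearson or Spearman coefficients do not fit an eight-category nominal location variable.

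The checks on variance inflation and the ridge penalty address unstable estimates. They do not change which variables are conditioned on. Finally, an analysis plan that is not shown may contain further models. The point therefore concerns what the article fixes, not what it leaves out.

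**Conclusion.** The point holds for tumor location and KPS, and rests on a possible path through depression. The model described answers a conditional question where the Perspective asks a broader one. This is a matter of estimand and interpretation in an exploratory study; it does not invalidate the full model.

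The size is unknown. With the assumed total effect of 0.30, the adjusted KPS coefficient lies between 0.30 and 0, depending on the mediated share. It would be tempting to quote one large percentage loss, but any such figure rests on assumed paths, and with no mediation almost nothing is lost. The planned ridge fit would also give somewhat different numbers from these unpenalized ones. For social support and marital status the documents give no basis for a direction.

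**What to change.** Prespecify two models.

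1. Demographics, time since diagnosis, tumor location, KPS and social support, without PHQ-8, GAD-7 and HRQoL (about 15 parameters). GAD-7 and HRQoL are left out along with PHQ-8 because, where they correlate with depression, they would partly stand in for it.
2. The full model as now planned, which serves the depression and anxiety objective.

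Report both, and label the coefficients as associations before and after adjustment for mood and HRQoL. Use the first model to answer the location and KPS question. Location is still conditional on KPS there, so either say so or also show location without KPS. For social support and marital status, present both models without assuming a direction. State that no factor will be reported as unassociated with suicidality on the full model alone.

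The cost is one extra model to fit and report, from data already collected, with no larger sample. Fixing it before results are seen also prevents a later choice between the two.

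### The multivariable model is fitted by cross-validated ridge, yet coefficients with 95% confidence intervals are promised with no other fit or suitable interval method named; on the natural reading these intervals fall well short of 95% coverage for real associations

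*Protocol article*

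**What the plan says.** The third paragraph of Statistical analyses (protocol article, Methods) runs in this order:

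- The model: "all prespecified candidate predictors will be entered simultaneously into a multivariable model without prior univariable screening".
- The estimator: "penalized regression (ridge regression with tuning via cross-validation) will be applied", with reduced overfitting and more stable estimates given as the reason.
- The bootstrap: "Model performance will be internally validated using bootstrap resampling (e.g., 5,000 resamples) to estimate and correct for optimism in performance metrics".
- The report: "Regression coefficients with 95% confidence intervals will be reported, along with model performance measures".

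The Sample size calculation section concedes that effects may be smaller than assumed and gives this as the safeguard: "all analyses will report confidence intervals and effect size estimates alongside significance tests to allow for an informed interpretation of the findings".

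The Perspective section sets the primary objective as modelling associations of the SSEV score with depressive symptoms, anxiety and the other prespecified characteristics. That is a question about coefficients, not about prediction.

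The first paragraph of Statistical analyses also names linear regression, or generalized models if the score is markedly skewed or zero-inflated, with residual checks and variance inflation factors. No sentence says which fit supplies the intervals.

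**The concern.** Cross-validation chooses the ridge penalty to minimise prediction error, and it does so by accepting bias towards zero. An interval built from a standard error or from bootstrap percentiles is centred on the shrunken value and makes no allowance for that bias. With correlated predictors, ridge also moves part of a true effect onto its neighbours. PHQ-8, GAD-7 and the EORTC quality-of-life scores can be expected to correlate, so the problem would be largest where the study is most interested.

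The planned bootstrap does not repair this, because it is assigned only to optimism in the performance metrics.

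If the intervals do come from the ridge fit, true correlates of suicidality would be understated with error bars that are too narrow and in the wrong place. A null variable correlated with a true correlate could also appear associated. The article relies on these intervals for interpretation and hopes that the identified correlates will inform screening pathways.

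**Working it through.** **1. The plan's own figure.** From Sample size calculation: f² = 0.15, about 20 parameters, alpha 0.05, power 0.80. R² = 0.15/1.15 = 0.13. For the overall F test of an unpenalised linear model, noncentrality = f² × N = 0.15 × 157 = 23.55, with 20 and 157 − 21 = 136 degrees of freedom. Power is 0.803, and 157 is the smallest N that reaches 0.80 (19 parameters give 153, 21 give 160). The stated 157 reproduces exactly, as a calculation for the unpenalised model.

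**2. Size of the shrinkage, by hand.** For standardised, uncorrelated predictors, the ridge estimate is roughly the true coefficient times N/(N + λ). Take unit error variance and all the signal in one predictor, so b = √0.15 = 0.387. The median cross-validated penalty in the simulation below was λ = 144.

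- Shrinkage factor: 157/(157 + 144) = 0.52.
- Expected estimate: 0.387 × 0.52 = 0.20, a bias of about −0.185 (simulated: −0.184).
- Approximate standard error at that penalty: √157/(157 + 144) = 0.042, so the interval half-width is about 1.98 × 0.042 = 0.08.

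The bias is more than twice the half-width, so the interval will usually miss the true value.

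**3. Simulated coverage.** From the document: N = 157, 20 predictors, R² = 0.13. Assumed: R² = 0.30 as a second case; normal errors; five predictors correlated at 0 or 0.6; signal in one, three or all 20 predictors. The penalty was chosen by 10-fold cross-validation, with 400 trials per row. Entries are the percentage of nominal 95% intervals that contain the true value, averaged over the non-zero coefficients. The bootstrap holds the penalty fixed.

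| R² | Correlation | Signal in | Least squares | Ridge, Wald | Ridge, percentile bootstrap |
|---|---|---|---|---|---|
| 0.13 | 0 | one | 93.0 | 19.3 | 15.0 |
| 0.13 | 0 | three | 94.9 | 43.0 | 36.9 |
| 0.13 | 0 | all | 95.2 | 70.2 | 66.0 |
| 0.13 | 0.6 | one | 97.8 | 6.2 | 4.3 |
| 0.13 | 0.6 | three | 95.7 | 29.3 | 26.7 |
| 0.13 | 0.6 | all | 95.1 | 67.3 | 63.0 |
| 0.30 | 0 | one | 94.0 | 38.0 | 29.2 |
| 0.30 | 0 | three | 95.8 | 66.6 | 60.2 |
| 0.30 | 0 | all | 95.0 | 88.1 | 84.2 |
| 0.30 | 0.6 | one | 95.8 | 16.8 | 13.0 |
| 0.30 | 0.6 | three | 95.3 | 47.4 | 42.0 |
| 0.30 | 0.6 | all | 94.9 | 85.5 | 82.1 |

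**4. Re-tuning the penalty in every resample.** One scenario (R² = 0.13, correlation 0.6, signal in three; 100 trials) gave 78% on average and 64% for the strongest predictor. With the penalty held fixed, the same run averaged 23%. Re-tuning helps but does not restore 95%. Further runs with re-tuning, at R² of 0.13 to 0.30, gave 50% to 85%.

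**5. Null coefficients.** Averaged over all nulls in step 3, ridge coverage was 88% to 95%. The loss sits in nulls correlated with a true correlate. In a further run (N = 157, R² = 0.13, four predictors correlated at 0.65, one of them and two independent predictors non-zero; 300 trials, fixed penalty), the strongest coefficient averaged 0.114 against a true 0.305, with 8% coverage. Its correlated nulls had 74% to 77% coverage, so their intervals excluded zero in 23% to 26% of trials. Across most runs, correlated nulls had about 72% to 87%.

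**The case against.** The strongest reply is that the premise is inferred. The first paragraph of Statistical analyses names linear or generalized models, and its residual checks and variance inflation factors belong to an unpenalised fit. The significance tests are promised in Sample size calculation for all analyses, where ridge is not mentioned. The article is condensed, and an analysis plan that is not shown may specify an unpenalised fit or a bias-corrected interval. This stands in part: a reader might infer that the protocol commits itself to ridge intervals and ridge tests, and the text does not say so outright. It does not remove the point, because ridge is the only estimator that the paragraph gives for the multivariable model, and the intervals are promised in that same paragraph.

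Second, the percentages rest on assumed correlations, signal patterns and normal errors, and the lowest ones come from holding the penalty fixed. That is correct, and no single percentage should be quoted as the error of this study. The direction did not change in any pattern tried.

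Third, ridge has a stated purpose and the work is labelled exploratory. In one check, root mean squared error over all 20 coefficients was 0.065 for ridge against 0.090 for least squares, although ridge was worse on the non-zero ones. This supports ridge for stability and prediction. It does not support attaching a 95% label to intervals around its coefficients.

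A reader might also infer that false associations would be common throughout. The figures do not show that: nulls unrelated to any true correlate are nearly right.

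**Conclusion.** The point holds in conditional form. The article fixes ridge as the estimator of the multivariable model, promises 95% intervals for coefficients, and names neither another source nor a method that allows for shrinkage. If the intervals come from the ridge fit by standard or percentile-bootstrap methods, coverage for non-zero associations is roughly 5% to 90% under the scenarios tried, against about 92% to 98% for least squares. Correlated nulls are affected as well.

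These figures assume about 157 analysed patients, 20 parameters, R² of 0.13 to 0.30, normal errors, and correlations and signal patterns that the documents do not give. A skewed or zero-inflated SSEV score was not simulated. The sample size is untouched, since it was computed for an unpenalised test. Because associations are the primary objective and the intervals carry their interpretation, the ambiguity should be settled before analysis.

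**What to change.** State that coefficients, 95% confidence intervals and tests come from the unpenalised prespecified model: linear, or the generalized model chosen for the SSEV distribution. Alternatively, name a bias-corrected interval method for the penalised coefficients. Keep ridge with bootstrap optimism correction for predictive performance (R², RMSE) only. Taking the associations from the unpenalised model also matches the model behind the sample size.

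Robust standard errors should not be added without qualification. Brainstem, cerebellar and spinal locations may be sparse (an assumption). With 2, 3 or 5 patients in a category (N = 157, 20 predictors, 3,000 replicates), HC1 intervals covered 74%, 82% and 89%, and HC3 intervals 87%, 91% and 94%. If robust errors are used, choose a small-sample version and pool very sparse location categories by a prespecified rule.

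The cost is a few sentences, one extra model fit and wider intervals. Recruitment and data collection do not change.
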